### Study settings

As the quality of medical care in China is unbalanced distributed, we will carry out the study in hospitals respectively representing low (county hospitals), medium (small tertiary hospitals) and high levels (big tertiary hospitals with ACs) of anticoagulation management in Hunan province to comprehensively evaluate the SMART model. Three hospitals of each level are randomly selected, thus finally nine hospitals are included in this study. Our hypothesis is that the SMART model is not only better than the usual care (UC, physician managed clinics) and the AC management, but also could be applied in different levels of hospitals in China.

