### Procedures

#### Training health care providers

All the participated health-care providers from nine hospitals will be organized together to receive both face-to-face seminar training courses and online meetings to master the study protocol and the measurements of managing patients. Table 1 shows the detailed training courses. In each hospital, a multidisciplinary team consisting of a physician and a pharmacist will manage their patients in the SMART model group together. For the three county hospitals, experienced pharmacists who manage the anticoagulation clinics in the tertiary hospitals will also join their multidisciplinary team to help manage patients with the aim of assuring patients’ safety.

**Table 1 Tab1:** Training courses for health care providers from participated hospitals

Training courses	Details
**Warfarin management**	1.Theoretical knowledge ① Basic knowledge of warfarin ② The standard protocol of warfarin management with patient self-testing ③ Warfarin monitoring and dosing at different situations ④ Adverse events treatment, including thrombosis, minor bleeding and major bleeding ⑤ Introduction of new oral anticoagulants ⑥ Laboratory tests interpretation ⑦ Patient education on warfarin, including medication adherence, drug/food interactions, diet, exercise and mental health 2. Practice in simulate patients 3. Tests to assess participant’s theoretical knowledge and practice skills
**Related-disease management**	1.Theoretical knowledge ① Atrial fibrillation ② Valvular heart disease ③ Deep venous thrombosis and pulmonary embolism ④ Stroke ⑤ coronary heart disease 2. Practice in simulate patients 3. Tests to assess participant’s theoretical knowledge and practice skills
**SMART Model**	1.Theoretical knowledge ① Usage of the POCT device ② Usage of the “XY” app ③ Stratified management based on patient risks ④ Communication skills with patients via the “XY” app ⑤ Communication between local hospitals and tertiary hospitals ⑥ Patients’ referral 2.Practice in simulate patients 3. Tests to assess participant’s theoretical knowledge and practice skills

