#### Randomization

In low and medium level hospitals, only the UC group is used as the control group, thus eligible patients on warfarin will be randomly assigned to either the SMART model group or the UC group. While in the high level hospitals, both AC and UC are used as the control groups, thus eligible patients will be randomly allocated to the SMART model group, the AC group or the UC group. For each level of the three hospitals, a total of 120 patients in each arm will be enrolled. The flow chart of patients’ grouping and allocation is shown in Fig. 2. Patients’ randomization will be carried out by research staff using a standard protocol available in the website (http://stattrek.com/statistics/random-number-generator.aspx).

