### Outcomes

#### Primary outcome measure

The difference in TTR between the SMART model group and the control group during the 12 month period of study.

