#### Data analyses

We will report continuous variables as means ± SD and categorical variables as proportions. Data will be checked for normal distribution by means of the Kolmogorov–Smirnov’s test. In compliance with the distribution of data, Student’s t-test or Mann–Whitney’s U-test will be used for comparisons between the SMART model group and control group. Chi-square or Fisher’s exact tests will be used to compare between the SMART model group and control group with respect to categorical data. The control of anticoagulation will be assessed by evaluating TTR with the Rosendaal method [18] in each arm. The follow-up assessment data will be analyzed using Generalized Linear Mixed Model and survival analysis. *P* ≤ 0.05 is considered statistically significant. All tests are two tailed. From the perspective of health-care payer, we will conduct a cost-effectiveness analysis to assess the economic impact of the SMART model for warfarin home management. A Markov model, a half-cycle correction and a discount of 5% will be constructed or used to estimate the total costs and quality-adjusted life-years (QALYs) over the 2-year period (the outcomes beyond the observation period will be predicted according to the results obtained in the study). We will collect the direct and indirect costs of each enrolled patient on warfarin, evaluate their quality of life through EQ-5D-3L utility value from data provided by patients, calculate QALYs, and analyze the effects of multiple variables by the Linear Mixed Effects Model. The direct costs include laboratory INR test fees in the control groups (or POCT fees in the SMART model group), outpatient clinic visit fees (or supervision fees in the SMART model group), hospitalization fees and emergency room visit fees. The indirect costs include deducted income due to absence of working, traffic fees and accommodation fees. Because warfarin is very cheap, the medication fee of warfarin is not calculated in each group. The incremental cost effectiveness ratio (ICER) will be calculated according to the total costs and QALYs, and one-way and probabilistic analyses will be performed to verify the stability of the model.

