Nevertheless, the implementation of warfarin home management faces obstacles in developing countries, including legal and regulatory issues, patients lacking direct and timely access to professional recommendations from health care providers, lack of access to telehealth technology, and limited or no coverage of the POCT device from the government. The current proposed study will take several measurements (the SMART model) to ensure its implementation in China, including using a mobile phone app to assist caregivers managing warfarin more efficiently, establishing medical alliance and multidisciplinary teams to manage patients together to solve the problem of maldistribution of medical care, and using a hierarchical strategy to manage patients to assure their safety. As far as we know, this proposed study will be the biggest multi-center randomized controlled trial to investigate the safety, effectiveness and cost-effectiveness of warfarin home management in China. If our final data demonstrate the SMART model for warfarin home management is cost-effective, this pattern may be applied in more provinces and be expanded to other chronic diseases management.

In the proposed study, we will include hospitals with different qualities of medical service. On the one hand, as the current medical service level in the county hospitals is low, we expect that the differences in TTR, numbers of under-coagulation or over-anticoagulation, and serious adverse clinical events between the SMART model group and the control group may be significantly bigger than the other two levels of hospitals. On the other hand, patients’ quality of life and costs on warfarin management may be improved the most obviously in the big tertiary hospitals, as patients do not have to travel long way to the hospitals.

The biggest limitation of our proposed study is that the nature of the intervention method (the SMART model) excludes patients who are unable to use a POCT device correctly, or fail to report their INR results through a mobile phone based app.

In summary, we have developed a novel model (the SMART model) to investigate the safety, effectiveness and cost-effectiveness of warfarin home management in different areas of Hunan province in China. This model may be particularly useful to manage patients on warfarin during and after the COVID-19 pandemic.

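### The only SMART-versus-control test named for continuous outcomes ignores hospital, although patients are randomised within nine hospitals and one team per hospital manages the SMART patients

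*Protocol article*

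**What the plan says.** The primary outcome is "The difference in TTR between the SMART model group and the control group during the 12 month period of study" (Primary outcome measure). For continuous variables the Data analyses section names one two-group method: "Student’s t-test or Mann–Whitney’s U-test will be used for comparisons between the SMART model group and control group", the choice depending on a normality check. Neither test has a term for hospital or level.

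The same section assigns data from the follow-up assessments to a generalised linear mixed model and survival analysis, and names a linear mixed effects model in the cost and quality-of-life analysis. Neither model is assigned to the primary TTR comparison, and neither is given a hospital or team effect.

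On the design:
- Study settings: "Three hospitals of each level are randomly selected, thus finally nine hospitals are included in this study". The stated hypothesis includes that the SMART model is usable across hospital levels in China.
- Randomization: individual patients are allocated, and "For each level of the three hospitals, a total of 120 patients in each arm will be enrolled". The arms on offer depend on level, since "in the high level hospitals, both AC and UC are used as the control groups".
- Training health care providers: "In each hospital, a multidisciplinary team consisting of a physician and a pharmacist will manage their patients in the SMART model group together". In the county hospitals, "experienced pharmacists who manage the anticoagulation clinics in the tertiary hospitals will also join their multidisciplinary team".
- Discussion: for the county hospitals, the authors expect that differences in TTR and other outcomes "between the SMART model group and the control group may be significantly bigger than the other two levels of hospitals".

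**The concern.** The test treats all patients in an arm as one independent sample. The design departs from that in two ways, with opposite effects.

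1. **Shared hospital effects.** Hospitals were chosen to represent low, medium and high quality of anticoagulation care, so mean TTR is likely to differ between them. Because randomisation is within hospital, such differences largely cancel from the SMART minus UC contrast. The unadjusted test still counts them as noise, so its standard error is too large and precision is lost.

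2. **Team effects in the SMART arm.** One physician-pharmacist team per hospital handles that hospital's SMART patients, and TTR depends on its dosing advice. A good or poor team moves about 40 patients together. If the result is to be carried to other hospitals, this variation belongs in the standard error, and the unadjusted test leaves it out.

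At stake are the width of the primary confidence interval and the support for the claim that the model works across hospital levels. Both problems exist for SMART versus UC alone; they do not depend on how the anticoagulation clinic arm is handled.

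**Working it through.** **The plan's own figure.** The sample size section gives 31 per group for a 5-point difference, 80% power and P = 0.05, with no SD. Solving n = 2(1.96 + 0.84)² SD²/5² for n = 31 gives SD = 5 × √(31/2)/2.80 ≈ 7.0 points. With 10% added, 31 × 1.10 = 34.1, matching the stated 34. The formula treats patients as independent. The planned 360 per arm is far above 34, so the issue is the standard error rather than the stated power.

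**Inputs for the check.** From the documents: 9 hospitals, 120 per arm per level, 360 SMART and 360 UC, two-sided 0.05. Assumed: an even split of 120/3 = 40 per arm per hospital, and all ICCs, since none is given.

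**(a) Shared hospital effect only, ICC ρh.** With total variance 1, the true variance of the difference is 2(1 − ρh)/360. The t-test expects about 2[(1 − ρh) + ρh × (8/9)(360/359)]/360.
- ρh = 0.05: ratio 0.95/(0.95 + 0.05 × 0.891) = 0.955. The true standard error is √0.955 = 0.977 of the t-test's, and the false-positive rate is 2[1 − Φ(1.96/0.977)] = 4.5%. Simulations gave 4.3% to 4.6%.
- ρh = 0.20: ratio 0.80/(0.80 + 0.20 × 0.891) = 0.818, square root 0.904, closed-form rate 3.0%. Simulation gave 3.2%.
- Simulated power, t-test against a hospital-adjusted model: 80.6% v 81.9% at ρh = 0.05, and 83.1% v 87.8% at ρh = 0.20.

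**(b) Team effect in the SMART arm only, ICC ρt, null of zero average effect over a population of teams.** The variance is understated by the factor F = [(1 + 39ρt) + 1]/2, and the false-positive rate is 2[1 − Φ(1.96/√F)].

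| ρt | F | √F | Closed form | Same, with ρh = 0.05 added |
|---|---|---|---|---|
| 0.01 | 1.195 | 1.093 | 7.3% | 6.8% |
| 0.02 | 1.390 | 1.179 | 9.6% | 9.1% |
| 0.05 | 1.975 | 1.405 | 16.3% | 15.9% |

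Simulations with ρh = 0.05 gave about 7%, 9% and 16%. The Mann-Whitney test behaved about the same. A t-test on the nine hospital-specific differences stayed near 5%.

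**(c) What a test that allows for team variation costs.** Assume SD 20, a 5-point effect and ρt = 0.02. The hospital-level test has about 70% power. The unadjusted t-test rejects about 88% of the time, but at a true alpha near 10%. Within one level (3 hospitals, 2 degrees of freedom) the figures are about 17% and 49%. With no team variation but true level effects of 10, 5 and 0 points, a hospital-level test without an arm-by-level term falls from about 85% to about 60%, because fixed level differences are counted as random variation.

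**The case against.** Several counter-arguments have force.

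- **The sentence on tests is generic.** It does not name TTR, and INR values are collected at follow-up, so the mixed model might be meant for TTR. A reader might infer that the protocol firmly commits the primary analysis to a t-test; the text does not go that far. But it assigns the mixed model to no particular outcome and gives it no hospital term. The t-test or Mann-Whitney sentence is the only one that names a SMART-versus-control comparison of continuous data. This is a stated method that does not fit the design, not a detail merely left for later.

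- **Randomisation is within hospital.** If SMART has no effect in any hospital, the unadjusted test is slightly conservative, not liberal. This stands. A reader might infer that the test simply has a 16% error rate. That figure needs an assumed team ICC of 0.05 and a null about a wider population of teams. With SD 20, that ICC means a team SD of √0.05 × 20 ≈ 4.5 points, nearly the whole 5-point target effect.

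- **Team variation is not something the authors predict.** The Discussion expects differences between hospital levels; it says nothing of teams within a level. Common training and common management rules may reduce team variation. Tertiary pharmacists joining the county teams also make it unclear that there are nine independent clusters.

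- **A random SMART-by-hospital effect is not the only valid primary analysis.** This also stands. It costs considerable power, and without an arm-by-level term it absorbs the level differences that the authors do expect.

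What survives is that hospital is part of the design and the named test leaves it out. The generalisation claim also needs an analysis that lets SMART effects vary by hospital.

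**Conclusion.** The point holds in a limited form. The unadjusted comparison disregards within-hospital randomisation. With only shared hospital effects it is mildly conservative: about 4.4% instead of 5% at an assumed hospital ICC of 0.05 and 3.2% at 0.20, with about 1 and 5 power points lost near 80%. For inference beyond the nine hospitals, which the random selection and the stated hypothesis invite, the error runs the other way: about 7%, 9-10% and 16% at assumed team ICCs of 0.01, 0.02 and 0.05. Every one of these figures rests on assumed ICCs and on 40 patients per arm per hospital.

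Two stronger readings are not supported: that the false-positive rate is known to be inflated, and that the random SMART-by-hospital model must be the primary test. The documents give no ICC and predict no variation between teams within a level, and a hospital-adjusted comparison is a valid primary analysis for the hospitals in the trial.

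**What to change.** In Data analyses, replace the unadjusted test for 12-month TTR with a linear or linear mixed model containing arm and hospital, with hospital nested in level. State that this is the primary analysis, and that the contrast is SMART versus UC, the control used at all three levels.

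As a supporting analysis for the claim about different hospital levels, report the nine hospital-specific SMART minus UC differences. Add a model with an arm-by-level term and a random SMART-by-hospital effect, using small-sample degrees of freedom such as Kenward-Roger.

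The change needs no new data and no extra patients. The hospital term uses a few degrees of freedom out of 720 patients and costs essentially nothing. It does not by itself deal with team variation, which is why the supporting model is needed. That model's price is wider intervals and few degrees of freedom, severely so within a single level of three hospitals, so it should inform the generalisation claim and not be imposed as the only primary test.

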In China, the percentage of time in therapeutic range (TTR, a tool of measuring warfarin treatment effects) was less than 40%, which was significantly lower than that of 62% in western countries [4]. Clinical observation studies found that warfarin associated ischemic stroke and intracranial bleeding were respectively 5.23 and 2.94% in patients from China, significantly higher than patients from the rest of the world (2.94 and 0.63%, respectively) [5]. In warfarin-treated patients in China, the median in-hospital direct cost per patient was about $3, 000 for thrombosis and $4, 500 for intracranial hemorrhage [6]. These data suggest that warfarin management in China needs further improvement. An investigation study launched by the PI using the Andersen’s Health Services Utilization Behavioral Model in 469 patients on warfarin indicated that long time and high cost for travel, low family income, low quality of warfarin monitoring and dosing in local hospitals were dominant reasons for missing follow-ups (data not published yet).

Anticoagulation clinics (AC) have been proved safer and more effective than usual care in warfarin management [7, 8], but there are only about 50 ACs located in big cities of China (mainly run in a physician-pharmacist cooperative AC pattern) at present. The number of ACs is too low, and it is not easy to open more ACs due to limitation of health care professionals and longtime education.

Point-of-care testing (POCT) device designed for measuring INR by patients or their families was first developed in 1980s in America [9] and then widely used in many developed countries. Compared to traditional laboratory INR test in outpatient clinics, POCT has great advantages in convenient home testing and fast result reporting. Soon patient self-testing (PST) for warfarin home management by using POCT devices and telehealth has been rapidly applied in developed countries. Although the PST model of warfarin management has demonstrated improvement of clinical outcomes compared to usual care clinics and anticoagulation clinics [10], it is rarely applied in developing countries, including China.

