## Methods/design

### Study design

This is a multi-center randomized controlled trial. We will carry out the study in three large tertiary hospitals with anticoagulation clinics, three small tertiary hospitals and three county hospitals in Hunan province of China. Eligible patients will be randomly assigned to the SMART model group or the control group (usual care clinic and anticoagulation clinic). Patients in the SMART model group do PST at home once every two to 4 weeks. Control patients receive usual care without intervention. All the patients will be followed up through outpatient clinics, phone call or online interviews at the 3rd, 6th, 9th and 12th month. The percentage of time in therapeutic range (TTR), incidence of warfarin associated major bleeding and thromboembolic events and costs will be compared between the SMART model group and control groups. Figure 1 describes the study design.

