#### Secondary outcome measures

The numbers of INR results indicating excessive under-coagulation or over-anticoagulation (INR < 1.5 or INR > 5.0).Serious adverse clinical events (clinical relevant non-major bleeding, major bleeding, thrombosis or death)Patients’ quality of life.Costs on warfarin management.

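### The general t-test/Mann-Whitney rule covers the secondary cost outcome by default, the plan does not say which analysis decides that comparison, and Mann-Whitney does not test mean cost

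*Protocol article*

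**What the plan says.** Secondary outcome measures lists "Costs on warfarin management". Study design says that the incidence of major bleeding and "thromboembolic events and costs will be compared between the SMART model group and control groups".

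Data analyses in the protocol article makes these statements that bear on cost:

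- Description: "We will report continuous variables as means ± SD and categorical variables as proportions".
- Choice of test: "Data will be checked for normal distribution by means of the Kolmogorov–Smirnov’s test". Depending on the result, Student's "t-test or Mann–Whitney’s U-test will be used for comparisons between the SMART model group and control group". No outcome is named or exempted.
- Repeated data: "The follow-up assessment data will be analyzed using Generalized Linear Mixed Model and survival analysis". Table 3 collects costs at baseline and at months 3, 6, 9 and 12, so cost is part of the follow-up data.
- Economic analysis: patient costs and EQ-5D-3L utilities are collected, a linear mixed effects model examines the effects of several variables, and "The incremental cost effectiveness ratio (ICER) will be calculated according to the total costs and QALYs", with one-way and probabilistic sensitivity analyses.

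Direct costs combine test and visit (or supervision) fees with hospitalization and emergency fees. The Background gives the size of the rare items: "the median in-hospital direct cost per patient was about $3, 000 for thrombosis and $4, 500 for intracranial hemorrhage".

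No sentence says which of these analyses decides whether cost differs between the arms.

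**The concern.** The economic question is about mean cost per patient, because a payer's bill is the mean times the number of patients and the ICER is built from total costs. Mann-Whitney asks a different question: whether a patient in one arm tends to rank above a patient in the other. An admission costing $4,500 counts only as a high rank, so a small saving shared by most patients can outweigh a few large bills.

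Different cost shapes in the arms are plausible here. SMART replaces laboratory and clinic fees with self-testing and supervision fees for every patient and aims to reduce travel, while admissions affect few patients. The rank test could then report lower cost under SMART although mean cost is equal or higher, or miss a saving that comes from preventing admissions. The report would carry a p-value that disagrees with the means printed beside it.

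**Working it through.** **1. Does the rule reach cost?** Cost is continuous, is a secondary outcome and is to be compared between groups. The rule covers comparisons of continuous data between SMART and control without exception. So it applies by default, alongside the mixed models.

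**2. Inputs.** The plan has no cost calculation to reproduce.

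- From the documents: event costs of about $3,000 and $4,500 (Background); 120 patients per arm at each hospital level, with 360 SMART and 360 usual-care patients overall (Randomization, Abstract); two-sided 0.05.
- Assumed: routine cost lognormal with mean R of $200 or $400 a year and CV of 0.5 or 1.0 (σ² = ln(1 + CV²)); admission probability p = 6% in control; each admission uniform on $3,000 to $4,500, mean $3,750; Kolmogorov-Smirnov cut-off 0.05 with mean and SD estimated from the data.

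**3. Equal-mean scenarios.** Mean cost = R + p × 3,750.

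- Control, R = 200: 200 + 0.06 × 3,750 = $425.
- SMART, routine $20 lower: p = (425 − 180)/3,750 = 6.53%, mean $425.
- SMART, routine $40 lower: p = (425 − 160)/3,750 = 7.07%, mean $425.
- R = 400, routine $40 lower: control 400 + 225 = $625; SMART p = (625 − 360)/3,750 = 7.07%, mean $625.

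**4. Results.** 2,000 simulated trials per cell; Monte Carlo standard error at most √(0.25/2,000) = 1.1 percentage points.

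| Routine cost, CV | Routine saving | Mann-Whitney rejects, 120/arm | 360/arm | t-test rejects |
|---|---|---|---|---|
| $200, 0.5 | none (identical arms) | 5% | 4% | 4–5% |
| $200, 0.5 | $20 | 29% | 67% | 5% |
| $200, 0.5 | $40 | 83% | 100% | 5% |
| $400, 0.5 | $40 | 26% | 64% | 5–6% |
| $400, 1.0 | $40 | 10% | 22% | 5–6% |

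In the rows with a saving, virtually every Mann-Whitney rejection says that SMART is lower, although the means are equal. With a smaller saving relative to the spread ($400, CV 1.0, $20) the rates fall to 7% and 9%.

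**5. Unequal means, 360 per arm, R = 200, CV 0.5.**

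- SMART $50 dearer (160 + 0.084 × 3,750 = $475 against $425): Mann-Whitney declares SMART lower in about 100% of trials; the t-test does so in under 1%.
- SMART cheaper through halved admissions but $20 more routine cost: the saving is 0.03 × 3,750 − 20 = $92.50. Mann-Whitney rejects in about 40% of trials, essentially never in SMART's favour.

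**6. Another assumed shape.** Lognormal costs with equal means and log-SD 1.0 in SMART against 0.8 in control: the plan's rule declares SMART lower in 33% (120 per arm) and 74% (360 per arm) of trials; a Welch test rejects in 6–7%.

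**7. Routing.** In all routine-plus-admission scenarios of steps 3 to 5, Kolmogorov-Smirnov rejected normality in 100% of trials. With mild lognormal skew it rejected in 15% (120 per arm) and 89% (360 per arm) at log-SD 0.3, and in 2% and 29% at log-SD 0.2.

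**The case against.** The strongest reply is that the plan never says cost will be tested by Mann-Whitney. Cost is follow-up data, follow-up data go to a generalized linear mixed model, and such a model can compare means. The economic paragraph has its own linear mixed model and an ICER, and no rank test enters either. A condensed article may leave the choice of estimator for one secondary outcome to a fuller document. The simulated distributions are assumed, and the striking results need SMART to save on routine cost while having more admissions, whereas the article's Discussion expects fewer complications under SMART.

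Much of this stands. A reader might infer that the rule is the only or the deciding cost analysis; the text does not support that. A reader might infer that cost always goes to Mann-Whitney; that holds for the strong skew that rare admissions produce, not for mild skew. A reader might infer that the cost-effectiveness conclusion is invalid; the ICER does not use the rank test. Nor do the documents show that SMART will be wrongly declared cheaper, because they give no cost distribution and no evidence that its routine cost is lower once self-testing and supervision fees are counted.

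What remains is more than missing detail. The article states a test rule, exempts nothing from it, and that rule does not fit cost. The mixed-model sentences name no cost contrast and do not set the rule aside.

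**Conclusion.** The point holds in a limited form. The general rule reaches cost by default, its standing against the mixed models is left open, and costs with rare large admissions would be routed to a test that does not address mean cost. In the equal-mean scenarios tabulated, rejection runs from about 10% to 100%, against about 5% for a test of means. The range depends on arm size, routine cost, its spread and the size of the routine saving, all assumed except arm size. The problem is a mismatch of quantity, not a miscalibrated test, since identical distributions give about 5%. It matters only if the arms differ in the shape of the cost distribution, and it affects the reading of the secondary cost comparison, not the ICER.

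**What to change.** Add one sentence to Data analyses: cost and QALYs are exempt from the t-test/Mann-Whitney rule, and the between-group comparison is the difference in arithmetic mean cost per patient, whatever the distribution. Give it with a non-parametric bootstrap 95% confidence interval, or as the marginal mean difference from a gamma log-link GLM or from the generalized mixed model already named. State that this analysis decides the cost comparison, so that it and the ICER address the same quantity.

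No new data are needed. The drawback is a wide interval, because admissions are rare, so a cost saving becomes harder to claim.
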